### Exclusion criteria

2.5

Patients should be excluded if any one of the following criteria apply.

(1)Patients with a history of hypersensitivity to remimazolam or propofol.(2)Patients with egg or soybean oil allergies, acute angle-closure glaucoma, myasthenia gravis, serious disease complications, or a history of allergies.(3)Patients with an American Society of Anesthesiologists physical status of ≥IV, shock, or coma.(4)Patients who are deemed inappropriate for inclusion in the study.(5)Patients with impaired cognitive function.

### Discontinuation criteria

2.6

For individual study participants:

If the principal investigator or sub-investigator determines that continuation of the study is not feasible for any of the reasons listed below, the patient will be removed from this study. In such cases, the reason for discontinuation will be explained to the patient as necessary.

(1)Study participants declining to participate in the study or withdrawing their consent.(2)The principal investigator or subcontractor deciding that it is appropriate to discontinue the study.(3)The entire study plan being canceled.

Discontinuation, suspension, or termination of the trial:

If the Safety Monitoring Committee decides to stop the trial, the entire trial will be stopped.

### Outcome measurements

2.7

The assessment schedule is represented in Figure 2.

**Figure 2 F2:**
[figure not shown]
Schedule of enrollment, intervention, and assessment.

#### Primary endpoint

2.7.1

The primary endpoint to be examined in this RCT is the assessment of anterograde amnesia. This will be examined as the number of posters remembered among 4 posters 24 hours after surgery (see Figure S1, Supplemental Digital Content, which illustrates the pictures) shown after awakening from anesthesia. Specifically, after awakening from anesthesia and being able to say their names, patients are to be shown 4 posters.^[6]^

#### Secondary endpoints

2.7.2

(1)Retrograde amnesia, based on the number of events remembered from prior to the start of anesthesia – ambulatory entry, bed transfer, vein insertion, BIS monitor attachment to the forehead, and mask fitting – and whether the patient remembers the poster (see Figure S2, Supplemental Digital Content, which illustrates the numeric characters) shown before the induction of anesthesia.(2)The dose of analgesic medication administered from the time the patient returns to the ward until 24 hours after surgery.(3)Immediate postoperative pain numerical rating scale (NRS) values (see Figure S3, Supplemental Digital Content, which illustrates the NRS).(4)Pain NRS scores 24 hours after leaving the operating room.

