**Methods/design::**

The aim of this exploratory, open, propofol-controlled, single-center, randomized clinical trial is to examine the effect of remimazolam on postoperative memory retention and delayed regeneration. Seventy patients undergoing breast surgery will be included in the study. The patients will be randomly assigned to receive propofol or remimazolam as sedatives during surgery. The primary endpoint is the number of posters patients remember 24 hours after surgery (among 4 posters shown after awakening from anesthesia) as an assessment of anterograde amnesia. Secondary endpoints are retrograde amnesia, dose of analgesic given from the time the patient returns to the ward until 24 hours after surgery, immediate postoperative pain numerical rating scale scores, and pain numerical rating scale scores 24 hours after leaving the operating room. Recruitment will take place between October 2021 and March 2022 to achieve the target sample size.

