### Investigational drug

2.3

Remimazolam is a standard sedative commonly used in clinical practice. It is similar to the benzodiazepine-like drug midazolam, which is also widely used in clinical settings. Remimazolam differs from midazolam in that its metabolites have no pharmacological effects and its sedative effects disappear rapidly upon the discontinuation of administration. The study drug (remimazolam: mundipharma K.K., Tokyo, Japan) is initiated at 6 mg/kg/h, which is changed to 1 mg/kg/h after confirming sleep. During surgery, the dose should be adjusted as required in the range of 0.5 to 2 mg/kg/h with reference to the bispectral index (BIS) value.

The initial dose of control dug (propofol: Maruishi Pharmaceutical Co., Ltd, Osaka, Japan) is 3 μg/mL and is administered using a target-controlled infusion pump and is adjusted with reference to the BIS value.

While the patient is still unconscious, flumazenil should be administered 5 minutes after the surgery ends. Flumazenil is intravenously and slowly administered at an initial dose of 0.2 mg. If the patient's wakefulness level is not sufficiently achieved within 4 minutes after administration, an additional 0.1 mg should be administered. If necessary, 0.1 mg should be administered at 1-minute intervals, up to a total dose of 1 mg.

For concomitant medications, the usual dosage of fentanyl and remifentanil for intraoperative analgesia should be administered. The dosage of remifentanil should not exceed a maximum of 0.5 μg/kg/min. A contraindication that should be considered is that antihistamines should not be administered between the day prior to surgery and the day after surgery.

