#### Safety endpoints

2.7.3

1)Nausea assessed based on the dose of antiemetic medication used immediately after surgery and from the time of returning to the ward until 24 hours after surgery.2)Time to full awakening.3)The incidences of hypotension, bradycardia, rhabdomyolysis, and anaphylaxis.

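### The analgesic endpoint leaves out any dose given between the end of surgery and return to the ward, and the amount left out may differ by arm

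*Protocol article*

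**What the plan says.** The Protocol article, section 2.7.2 (Secondary endpoints), item 2, defines the endpoint as "The dose of analgesic medication administered from the time the patient returns to the ward until 24 hours after surgery". The abstract (Methods/design) gives the same window: "dose of analgesic given from the time the patient returns to the ward until 24 hours after surgery". The two statements agree.

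Two other endpoints reach into the interval that this one omits:

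- Section 2.7.2, item 3, is "Immediate postoperative pain numerical rating scale (NRS) values".
- Section 2.7.3 (Safety endpoints), item 1, assesses nausea by the "dose of antiemetic medication used immediately after surgery and from the time of returning to the ward until 24 hours after surgery".

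Section 2.7.3 also lists "Time to full awakening". Section 2.3 (Investigational drug) describes the intraoperative opioids ("the usual dosage of fentanyl and remifentanil for intraoperative analgesia should be administered") and a reversal agent at emergence ("While the patient is still unconscious, flumazenil should be administered 5 minutes after the surgery ends"). It does not describe analgesic treatment between the end of surgery and the ward.

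**The concern.** The counting window opens at an event that follows randomization and closes at a time tied to surgery. A dose given before the patient reaches the ward is not recorded under this endpoint or any other in the article. If such a dose also reduces the need for a later one, it removes part of the ward total as well as being left out itself.

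Ward return may depend on recovery from the sedative, and recovery is something the trial compares between arms. Both the length of the uncounted interval and the treatment given in it may therefore be related to the arm. A difference in ward dose could then partly reflect where analgesic was given rather than how much was needed.

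The plan treats the early period as relevant for pain and for antiemetics, and gives no reason for leaving analgesics out of it. The immediate pain score does not fill the gap. A low score could mean little pain or early treatment, and the article does not say whether the score is taken before or after any early dose.

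**Working it through.** The plan has no figure of its own to reproduce: section 2.10 states that no sample size calculation was done. The check is a comparison of windows, followed by an illustration.

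**Windows side by side**

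| Measure | End of surgery to ward return | Ward return to 24 h |
|---|---|---|
| Analgesic dose (2.7.2, item 2; abstract) | not counted | counted |
| Antiemetic dose (2.7.3, item 1) | counted | counted |
| Pain score (2.7.2, items 3 and 4) | immediate postoperative score | score 24 h after leaving the operating room |

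**Length of the window.** Counted time = 24 h − time from surgery to ward return. For assumed returns at 30, 60 and 90 minutes this is 23.5, 23.0 and 22.5 h. The change in length is small. What matters is whether doses are given in the omitted part, and the documents do not say.

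**Illustration of size**

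From the documents:
- 35 patients per arm (section 2.10)
- two-sided significance level of .1 (section 2.12.1)

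Assumed, with no source in the documents:
- SD of the counted dose: 1.2 doses
- equal true total postoperative use in the two arms
- mean arm difference in uncounted doses, d: 0, 0.1, 0.2 or 0.3 per patient (for example, one uncounted dose in 0, 10, 20 or 30 percentage points more patients in one arm)
- normal approximation for a difference of two means

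With equal totals, ward dose = total − pre-ward dose, so the arm difference in ward dose has size d.

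- Standard error in SD units: √(2/35) = 0.239
- Shift in SD units: d / 1.2
- Rejection rate: P(|Z + shift/0.239| > 1.645)

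| d (doses) | Shift (SD) | Shift / 0.239 | Rejection rate |
|---|---|---|---|
| 0 | 0 | 0 | 0.100 |
| 0.1 | 0.08 | 0.35 | 0.121 |
| 0.2 | 0.17 | 0.70 | 0.181 |
| 0.3 | 0.25 | 1.05 | 0.278 |

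For scale, the standardized difference detectable with 80% power at this size and level is (1.645 + 0.842) × 0.239 = 0.59 SD. The shifts shown are well below that.

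**The case against.** The case against has real force.

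- **Ward use is a coherent endpoint.** It is stated clearly, and identically in the abstract and the methods. Nothing obliges the analgesic and antiemetic windows to match, since one is a secondary endpoint and the other a safety proxy for nausea. This stands: the difference between them is an unexplained choice, not a contradiction.
- **Direction.** A reader might infer that the arm waking sooner, or having more pain at emergence, will appear to need less analgesic. The documents do not support this. An arm that wakes sooner may also reach the ward sooner, which shortens its uncounted interval and points the other way.
- **Existence of the doses.** A reader might infer that emergence pain is routinely treated before the ward. No section says so. The article gives no recovery-area stay, no pre-ward analgesic use and no arm difference in either. The point rests on a possibility.
- **Error rates.** A reader might take 12%, 18% and 28% as the trial's false-positive rates. They rest wholly on assumed inputs, and the rate stays at 10% if pre-ward use is equal. If the quantity of interest really is ward use, a difference in ward dose is a true difference in that quantity. The rates describe error only for a reader who takes the endpoint as total postoperative need.
- **Importance.** Section 2.12.1 puts descriptive statistics first and adds group comparisons only as supplementary information. No primary conclusion depends on this endpoint.

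These objections limit the claim but do not remove the omission. The blinding of assessors in section 2.9 does not remove it either, because it lies in the definition. Even with balanced arms, the descriptive mean would understate postoperative analgesic use if any is given before the ward, and section 2.12.1 intends these results to inform larger trials.

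**Conclusion.** The omission is certain from the text: analgesic given between the end of surgery and ward return enters no endpoint in the article. That it differs by arm is possible but not shown, and neither its size nor its direction can be derived from the documents. Under the assumptions set out above, the consequence ranges from none (rejection rate 10% when pre-ward use is equal) to about 28% (0.3 uncounted doses per patient more in one arm). Severity is low. The change is still worth making because it is cheap and takes away a possible arm-dependent omission.

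**What to change.** In section 2.7.2, item 2, and in the abstract, define the endpoint as the total postoperative analgesic dose from the end of surgery to 24 hours after surgery. This covers the same two periods that section 2.7.3 names for antiemetics. Also report the pre-ward part and the ward part. Section 2.7.3 names two periods but does not say that they are reported separately, so the separate reporting has to be written out for this endpoint.

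The ward part is the endpoint as now defined, so that result stays available. Sample size, visits and patient care do not change. The cost is one more field to extract from the anesthesia or recovery record, plus the change of wording.

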#### Safety endpoints

2.7.3

1)Nausea assessed based on the dose of antiemetic medication used immediately after surgery and from the time of returning to the ward until 24 hours after surgery.2)Time to full awakening.3)The incidences of hypotension, bradycardia, rhabdomyolysis, and anaphylaxis.

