### Study design

2.2

The standard protocol items for randomized trials guidelines were followed. The present study is an exploratory, open, propofol-controlled, single-center, randomized controlled trial (RCT) to compare the efficacy and safety of remimazolam with propofol. The study will be conducted by the Department of Anesthesiology and Critical Care Medicine, Kyushu University Hospital. In total, 70 patients aged 20 to 65 years will be randomly assigned to receive remimazolam or propofol as sedative anesthetic agent. The participants will be randomly divided into 2 groups using stratified block randomization. The study design is summarized in Figure 1 and available at URL (https://upload.umin.ac.jp/cgi-open-bin/ctr_e/ctr_view.cgi?recptno=R000052026)).

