### Adverse events

2.11

All adverse events (AEs) that occur between the day of surgery and the end of day 2 after surgery will be recorded. A serious AE is defined as any adverse reaction resulting in any of the following outcomes: a life-threatening condition, death, or a condition that requires inpatient hospitalization or prolongation of an existing hospitalization and threatens to cause disability. Any serious AE will be documented in the medical records and reported to the Clinical Research Board by the responsible investigator, in accordance with the Japanese governmental regulations. If necessary, the investigators will administer treatment for any AE occurring during the course of the study.

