#### Safety analysis

2.12.2

The subject of this analysis will be the safety analysis set. The incidence of each AE (hypotension, bradycardia, rhabdomyolysis, and anaphylaxis) will be compared between the anesthesia groups using the χ-square test or Fisher exact test.

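### Nausea is measured only by antiemetic dose; the number of patients with nausea and with vomiting should be reported beside it

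*Protocol article*

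**What the plan says.** Section 2.7.3 (Safety endpoints) of the protocol article lists nausea first and defines it by drug use: "Nausea assessed based on the dose of antiemetic medication used immediately after surgery". Drug use is counted a second time over the ward stay, up to 24 hours. The section names no nausea score, patient report or incidence. The same list treats four other events differently: "The incidences of hypotension, bradycardia, rhabdomyolysis, and anaphylaxis".

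Section 2.11 (Adverse events) states: "All adverse events (AEs) that occur between the day of surgery and the end of day 2 after surgery will be recorded".

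Section 2.12.2 (Safety analysis) states: "The incidence of each AE (hypotension, bradycardia, rhabdomyolysis, and anaphylaxis) will be compared between the anesthesia groups". Nausea and vomiting are not in that list. Either a chi-squared test or Fisher's test may be used for the comparison.

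Section 2.2 (Study design) describes the trial as open. Section 2.9 (Data collection) says that data and outcome assessors are blinded. It does not say whether the staff who decide on antiemetics are.

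**The concern.** Antiemetic dose records a treatment decision. It equals nausea only if every nauseated patient is treated, to the same degree, in both arms. Two things can go wrong:

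- **Untreated nausea disappears.** A patient who is nauseated but given no drug contributes a dose of zero, the same as a patient with no nausea.
- **Treatment decisions enter the comparison.** If those deciding on antiemetics know the arm and act differently, dose can differ between arms when nausea does not. Blinding the person who later records the dose does not remove this.

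The trial's stated purpose is to prepare larger trials. A planner who wants to know how often patients are nauseated after each drug cannot read that from a mean dose.

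**Working it through.** The plan states no nausea rate, effect or power, so there is no figure to reproduce. The check is on definitions, followed by a short illustration with assumed rates.

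**1. Is there a direct measure among the endpoints?** No. In Section 2.7.3, the four events given as incidences do not include nausea, and nausea has dose only. The four events named in Section 2.12.2 are the same four.

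**2. Does the adverse-event period cover the nausea period?** Yes. The nausea period runs from just after surgery to 24 hours after surgery, so it ends on day 1. Recording under Section 2.11 runs from the day of surgery to the end of day 2.

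**3. What does dose measure?** Write *p* for the share of patients with nausea, *t* for the share of those who are treated, and *d* for the mean dose among the treated. If antiemetics go only to nauseated patients (a simplification),

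mean dose = *p* × *t* × *d*.

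Only *p* is nausea. A difference between arms in *t* or *d* also moves the result.

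**4. Illustration.** All rates are assumptions. The product *p* × *t* is the share of patients with a dose above zero. It serves to show the mechanism and is not an endpoint of the plan.

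*Same treated share in both arms, true nausea 20% v 40%:*

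| *t* | *p* × *t* | Difference |
|---|---|---|
| 100% | 20% v 40% | 20 points |
| 75% | 15% v 30% | 15 points |
| 50% | 10% v 20% | 10 points |
| 25% | 5% v 10% | 5 points |

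The absolute difference shrinks in proportion to *t*. The ratio stays at 2.

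*Different treated shares, true nausea 30% in both arms:*

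| *t* by arm | *p* × *t* | False difference |
|---|---|---|
| 50% v 50% | 15% v 15% | 0 points |
| 40% v 60% | 12% v 18% | 6 points |
| 30% v 70% | 9% v 21% | 12 points |

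With 35 patients per arm (Section 2.10), 6 points is 0.06 × 35 = 2.1 patients and 12 points is 0.12 × 35 = 4.2 patients. At equal *d*, the mean doses would differ by a factor of 18/12 = 1.5 or 21/9 = 2.3, with no difference in nausea.

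**5. What would incidence add?** If the adverse-event record captures a share *e* of nausea cases, recorded incidence is *p* × *e*. This no longer depends on *t* or *d*, provided that nausea is asked about independently of treatment. It is a fair comparison if *e* is equal in the two arms. Section 2.11 does not state how events are elicited, so *e* is unknown.

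**6. Does the plan pair drug use with a direct measure elsewhere?** Yes, for pain. Section 2.7.2 lists analgesic dose together with pain NRS scores at two times. Nausea has only the drug-use half.

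**The case against.** The strongest reply is that using treatment as a proxy is a choice and not an error. Dose comes from a drug record, whereas an adverse-event record may be no better. Section 2.11 does not say that nausea is asked about, or that mild untreated nausea counts as an event. If staff note nausea mainly when they treat it, the untreated patient is missed again, and in an open trial staff-noted events are exposed to knowledge of the arm as well. This stands. It is why incidence should sit beside dose and not replace it, and why elicitation has to be alike in both arms.

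A second reply is that a condensed article need not list every table, and that Section 2.12.2 does not say other events will go unreported. This also stands: a reader might infer that nausea will not be reported as an adverse event at all, and the text does not support that. What the article does fix is the definition of the nausea endpoint and the list of events for between-group comparison. Nausea incidence is in neither.

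Other stronger readings are tempting and are not supported:

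- **That nausea incidence is already in hand for free.** Recording all adverse events does not show that nausea is fully captured.
- **That preventive antiemetics inflate the dose.** The article mentions no antiemetic prophylaxis, and the endpoint's periods are postoperative.
- **That those giving antiemetics know the arm.** The design is open, which makes this possible, but the article does not say who decides or what they know.
- **That the loss of power can be stated.** The documents give no rates, and the endpoint is a dose. A power figure for any antiemetic use would test a variable that the plan does not define, and would shift with the choice between the two tests allowed in Section 2.12.2.

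**Conclusion.** The point holds as a minor improvement. Nausea is defined only through antiemetic dose, which scores untreated nausea as zero and, in an open trial, may carry differences in treatment decisions between arms. The article already provides for an adverse-event record over the right period but does not use it for this endpoint.

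The size cannot be derived from the documents. The percentages under the check rest on assumed nausea rates and treated shares and show only direction and mechanism. The effect is confined to one safety endpoint in an exploratory trial whose sample size was set by feasibility. The primary endpoint is not affected.

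**What to change.** In Section 2.7.3, add the number and percentage of patients with nausea, and the number and percentage with vomiting, taken from the adverse-event record between end of surgery and 24 hours. Keep antiemetic dose as it stands, alongside these. In Section 2.12.2, add nausea and vomiting to the events compared between groups, with the tests already named there. State in Section 2.11 that nausea and vomiting are elicited in the same way in both arms.

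The cost is one or two extra table rows and a sentence on elicitation. If nausea is not at present asked about in a uniform way, doing so is a small added task for staff. The incidence remains only as complete as that elicitation. The change concerns measurement and reporting and leaves antiemetic treatment as it is.

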### Randomization

2.8

An allocation supervisor appointed by the Data Center of the ARO Clinical Research Promotion Department of Clinical and Translational Center has prepared an allocation table for the purpose of randomization. The electronic data capture software used in this study refers to this allocation table for randomly allocating patients. The allocation ratio was set at 1:1. The detailed procedure of random allocation has not been provided to the researchers. The permuted block randomization block method will be used for allocation.

### Data collection

2.9

Data will be recorded and stored via REDCap software (Nashville, TN) while the study is in progress, and the data will then be exported from the database into statistical software for analysis.^[7,8]^ REDCap, which allows for additional data privacy and security protections compared with other data storage platforms, has an audit trail that records every time a participant or staff member makes changes to any data entered on the website. The data used for this study, although not available in a public repository, will be made available in an anonymized and de-identified form to other researchers upon reasonable request. Data and outcome assessors are blinded.

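### The unqualified statement that outcome assessors are blinded is not credible for time to full awakening or for hypotension and bradycardia noted by the anaesthesia team during surgery

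*Protocol article*

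**What the plan says.** All references are to the protocol article.

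- **Data collection (2.9):** "Data and outcome assessors are blinded". No endpoint is excepted.
- **Study design (2.2):** the trial is an "exploratory, open, propofol-controlled, single-center, randomized controlled trial (RCT"). The abstract and the Discussion also call it open.
- **Investigational drug (2.3), remimazolam:** "the dose should be adjusted as required in the range of 0.5 to 2 mg/kg/h with reference to the bispectral index (BIS) value".
- **Investigational drug (2.3), propofol:** it "is administered using a target-controlled infusion pump and is adjusted with reference to the BIS value".
- **Investigational drug (2.3), end of the case:** flumazenil is titrated against wakefulness: "If the patient's wakefulness level is not sufficiently achieved within 4 minutes after administration, an additional 0.1 mg should be administered". Further doses may follow at 1-minute intervals.
- **Safety endpoints (2.7.3):** these include "Time to full awakening" and the incidences of hypotension and bradycardia. Section 2.12.2 compares those incidences between arms by a chi-square or Fisher exact test.
- **Primary endpoint (2.7.1):** the number of posters recalled 24 hours after surgery, out of 4 shown once the patient has awakened and can say their name.

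**The concern.** A statement of assessor blinding is a claim about how every outcome was obtained. Here it covers all endpoints alike, whereas the described conduct separates them into two kinds. Recall at 24 hours is obtained well after drug delivery has ended, by someone who need not have been in the operating room. Awakening, and haemodynamic events during surgery, arise while the treating team is giving or reversing a drug that it knows.

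At stake is how the safety results are read. Judging when a patient is fully awake, or whether a fall in pressure counts as hypotension, leaves room for expectation. The Introduction says that earlier Japanese trials reported a smaller haemodynamic effect with remimazolam than with propofol, so an expectation exists. The Discussion also gives time to full awakening a wider use, as a possible indicator of length of hospital stay in future outpatient endoscopy. The trial is meant to inform later large trials, so an inaccurate description of how these outcomes were assessed could be carried forward.

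**Working it through.** The plan has no figure to reproduce: section 2.10 states that no sample size calculation was done, and blinding is not a numerical property. The check sets the passages side by side, endpoint by endpoint.

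**1. Does an open design by itself contradict blinded assessors?** No. Treatment can be open to the treating team and hidden from a separate assessor. The question is whether the described conduct makes that plausible for each endpoint.

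**2. Who knows the arm?** The team running the infusion does. Section 2.3 gives the two drugs in different ways (mg/kg/h against a plasma-type target in μg/mL on a target-controlled pump) and asks the team to adjust each to BIS.

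**3. Which endpoints arise in that team's hands?**

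| Endpoint | What the article describes | Blanket statement credible? |
|---|---|---|
| Poster recall at 24 hours (primary) | Interview a day after surgery | Yes |
| Data review | Work on recorded data | Yes |
| Time to full awakening | Wakefulness judged during flumazenil titration, by those giving it | No, not without a separate observer |
| Hypotension, bradycardia during surgery | Occur while the team titrates a known drug | No, as first observed; yes, if derived blind from recorded vital signs |
| Hypotension, bradycardia later | Adverse events recorded to the end of day 2 after surgery (2.11) | Not determined by the article |
| Immediate pain NRS | Patient's own rating; place and collector not stated | Not a case of assessor judgement |
| Rhabdomyolysis, anaphylaxis | Place and assessor not stated | No basis for a conclusion |

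The awakening row is the clearest. Section 2.3 requires a judgement of whether wakefulness is sufficient 4 minutes after the first dose, and allows re-dosing at 1-minute intervals after that. The endpoint is timed over the same period. The argument does not depend on flumazenil revealing the arm, since section 2.3 does not restrict it to one arm. It rests on the judgement being made by staff who already know the arm.

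**4. Scale.** With 35 patients per arm (2.10):

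- one patient judged differently: 1/35 = 2.9 percentage points;
- three: 3/35 = 8.6 points; four: 4/35 = 11.4 points.

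The number judged differently is an assumption, as no document figure supports any value. As an illustration with assumed counts, 14/35 against 10/35 (40.0% against 28.6%) gives a two-sided Fisher p = 0.45. If four events in the second arm were not counted, 14/35 against 6/35 (40.0% against 17.1%) gives p = 0.063. That falls below the two-sided .1 level that section 2.12.1 sets for all analyses; section 2.12.2 names no other level. This shows how few classifications could matter at this sample size. It does not predict that they will be biased.

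**The case against.** The strongest reply is that an open trial with blinded assessors is a standard design, so sections 2.2 and 2.9 do not contradict each other. A separate observer could time awakening, and a blinded reviewer could read recorded vital signs. The article does not say who assesses these outcomes, where, or whether the pump is in that person's view. Such detail is commonly left to a full protocol, and its absence is no finding. This stands. A reader might infer that blinding is impossible for these endpoints; the documents do not support that.

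Four further inferences are tempting and also fail:

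- *That nearly every safety comparison is affected.* Nothing places the assessment of rhabdomyolysis or anaphylaxis with the anaesthesia team, and section 2.11 records adverse events to the end of day 2 after surgery, so even hypotension and bradycardia are not confined to the operating room. Early antiemetic use is a recorded dose; who prescribes it is a matter of care-provider blinding, which section 2.9 does not claim.
- *That immediate pain is assessor-biased.* The NRS is the patient's own score. Bias from a patient knowing the arm would be a different issue.
- *That the start of the poster display is left to staff discretion.* Section 2.7.1 already ties it to an observable event, the patient saying their name.
- *That the direction of bias is known.* The Introduction shows an expectation, not an effect of that expectation on recording.

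The consequence is also limited, because the primary endpoint is not affected and the study is exploratory. What the reply does not rescue is the missing qualification. The point challenges a sentence that the article states for all endpoints, while section 2.3 describes conduct that makes it doubtful for some of them.

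**Conclusion.** The concern holds in a limited form. The blinding statement is not supported by the described conduct for time to full awakening, or for hypotension and bradycardia observed by the treating anaesthesia team during surgery. It can stand for the 24-hour recall interview, and so for the primary endpoint, and for the data review.

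The conclusion rests on two inferences from section 2.3: that the team titrating the drug knows which drug it is, and that this team makes the observation unless a separate assessor is arranged. If the full protocol provides a separate blinded observer for awakening, or blinded adjudication of recorded vital signs, the statement would be accurate for those endpoints and would only need to say so.

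The size of any bias cannot be derived from the documents. The 2.9 points per patient is arithmetic; any number of misjudged patients is an assumption. The point deserves correction because the change is cheap and the affected results are compared between arms, not because the main result is in doubt.

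**What to change.** 1. In section 2.9, replace the blanket sentence with one naming the endpoints for which blinded assessment is actually arranged, for example the 24-hour recall interview and the data review.
2. Describe time to full awakening, and any other outcome recorded by the anaesthesia team, as unblinded, unless a separate blinded observer is in place; in that case, say so.
3. Derive intraoperative hypotension and bradycardia from the recorded vital signs by one rule, fixed before the data are seen and applied to both arms by a reviewer who does not know the arm. The rule concerns classification for analysis only and changes nothing in patient management.

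No new trigger for the poster display is needed.

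The cost is a wording change, a small data-derivation step, and a less favourable blinding statement in the report. Blind derivation removes judgement from the classification of events. It does not remove any influence of the open design on how the team manages blood pressure and heart rate, and the report should acknowledge that.
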